#### Field Studies

##### Recruitment

For every field study the eligibility criteria are 18 years of age and older, current smoker (any number of cigarettes per day), and English or Spanish speaker. We plan to recruit low-income participants (ie, those who have Medicare and/or Medi-Cal, the California state equivalent, or are uninsured). Six face-to-face field studies are planned.

##### Year 1

###### Field Study 1: Ethnographic Study of Naturalistic Smoking, Smoking Cessation Attempts, and Smartphone Use

We will use shadowing methods (observing smokers’ actual behavior in their natural environment) plus semistructured interviews to learn how smokers think about their smoking behavior, how they attempt to quit, and how they use their smartphones (ie, how they find, download, install, and begin using apps).

###### Field Study 2: Ethnographic Study of Smoking Cessation App Use

We will recruit SFHN patients who have installed at least one smoking cessation app on their smartphones. We will use shadowing and semistructured interviews to study the use of smoking cessation apps participants have installed on their own. We will ask participants to install the baseline version of our Web app and use it for one week, scheduling follow-up interviews to learn about use patterns and reactions to the baseline Web app.

###### Field Study 3: Participatory Design Field Test

We will schedule two meetings, one in English and one in Spanish, with 5 SFHN smokers each, with the purpose of jointly working on the design of an ideal app to help them stop smoking. Groups will be facilitated by research staff familiar with Web apps to keep the group focused on the intended product. The result will be a paper prototype and sample screens developed on tablets to ensure that we are accurately rendering the patients’ suggestions. In addition, we will schedule two meetings, one in English and one in Spanish, with 5 SFHN providers each (smoking cessation counselors, nurses, physicians), using the same procedure. The results of the four meetings will be shared with the development team as part of the creation of version 1.0.

##### Year 2

###### Field Study 4: Usability Field Testing for Version 1.0

Once the developers begin the design process, we will engage in iterative usability testing with 4 or 5 SFHN English speakers and 4 or 5 Spanish speakers. Their input will be incorporated in version 1.0, which will be subjected to limited online testing (Online Study 2).

###### Field Study 5: Usability Field Testing for Version 2.0

We will engage in iterative usability testing as version 2.0 is being developed to ensure that SFHN smokers have input into the new version, which will then be subjected to limited online testing (Online Study 3).

###### Field Study 6: Usability Field Testing for the Final Version of the San Francisco Stop Smoking Web App

We will carry out iterative usability testing of the final version to ensure that SFHN smokers have input. The final version will be tested in an RCT.

#### Online Studies

##### Online Study 1: Baseline (Usual Care) Web App

A Web app will be developed to test the data-gathering infrastructure for the subsequent apps and generate baseline information on four variables: recruitment rates, utilization of the app, follow-up completion rates, and quit rates. Usual care is described in the Intervention section. We will engage in focused recruitment of smokers from the SFHN (up to 25 English speakers and 25 Spanish speakers) as well as open online recruitment with California as our main target (up to 50 English speakers and 50 Spanish speakers). We will implement follow-up interviews to examine quit rates at 1, 2, and 3 months after enrollment in the study. We will use 3 text messages (identified as coming from the Stop Smoking Study) 2 days apart. The first question will ask “Have you smoked 1 or more cigarettes in the last seven days?” A no response will be interpreted as 7-day point prevalence abstinence. Additional questions will address 30-day abstinence, number of cigarettes smoked daily if not abstinent, and use of other smoking cessation tools.

##### Online Study 2: Version 1.0

We will implement the same procedure as Online Study 1. We will obtain suggestions from our field test participants as to how to increase recruitment rates, for example, by modifying the wording in our social media announcements, the themes we touch upon in our radio and television interviews, the flavor of our public service announcements, word-of-mouth recruitment, the use of text messages to encourage enrollment, the wording of our search engine ads, and so on. We will use “tokens,” as described below, to identify how the participant heard about the Web app. We will examine which of these sources yield the greatest increases in recruitment. We will also track overall recruitment, as measured by the speed with which we meet our recruitment goals.

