### Clinical Problem

We have argued that Internet interventions can help reduce health disparities by reaching those who do not have access to smoking cessation aids. Concerns have been raised that, although this approach may be increasing the reach of evidence-based smoking cessation interventions across large segments of the population and thus reducing health disparities across countries, digital interventions may actually increase health disparities. The reason for this concern is that more highly educated people may be more likely to use these interventions and perhaps more likely to benefit from them. To address this concern, we have compared quit rates for participants with differential socioeconomic standing as well as for participants from countries with different gross domestic products. We tested whether smokers in richer countries and smokers higher in self-reported SES are more likely to quit. Our results show that, indeed, our Internet interventions preferentially benefit individuals from countries with higher gross domestic products and/or with higher individual socioeconomic standing [24]. This may be due to reasons other than the availability of technology because all participants had access to the online intervention. It may be that the ways in which we have designed the interventions do not take into account the characteristics of smokers with lower incomes and lower educational levels. These findings are the motivation for the current study. We have received TRDRP funding to revise our smoking cessation digital tools so that they address the unique interests and needs of low-income and Latino smokers in California with the hope that the modifications made will generalize to other smokers from similar socioeconomic levels. We conceptualize the SFHN, described in the next paragraph, as serving as a “magnifying glass” that will allow us to learn how to best serve this population with our digital tools so that when we make the tools available worldwide, the range of smokers we will be able to reach and be effective with will be greater.

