#### Aim 2: Improvement of Dissemination Strategies

Input from SFHN patients will identify effective ways of reaching and encouraging low-income English- and Spanish-speaking smokers to use the digital smoking cessation interventions that are developed. This information will support ongoing dissemination and implementation efforts beyond the grant period.

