#### Hypotheses

H1: Utilization of the final smoking cessation Web app (number of screens viewed, time spent using app, and amount of data entry) will be significantly higher than that of the baseline Web app.

H2: Recruitment based on dissemination strategies derived from ethnographic interviews will reach a significantly higher number of participants for successive online studies.

H3: Abstinence rates (7-day self-reported abstinence) will be significantly greater for the final Web app than for the baseline Web app.

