##### Online Studies

To reduce participant burden, we will use reduced versions of the baseline and follow-up questionnaires we used in our earlier website-centered studies. Being asked to respond to long surveys on a mobile device is likely to result in high dropout rates. Therefore, we propose the following:

Eligibility: age, current smoker, speak English or Spanish.Baseline (obtained on the Web app when the smokers installs the app and gives consent to enter the study): demographics (age, sex, race, ethnicity, marital status, employment status, income, and educational level), smoking history (age first cigarette, age regular smoker, cigarettes per day, quit attempts, and methods used to quit), the Fagerström Test for Nicotine Dependence (6 items) [41], and rating of quit confidence.Follow-ups (brief and obtained using text messaging to increase completion rates): smoking status (7-day and 30-day point prevalence abstinence rates, operationalized as a “no” response to “Have you smoked 1 or more cigarettes in the last seven days?” and, if “no” to the previous question, “Have you smoked 1 or more cigarettes in the last 30 days?”); number of cigarettes per day smoked in the last week (if still smoking); and rating of confidence that the user will remain quit (if not smoking) or be able to quit in the next 30 days (if smoking).

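### Aim 2 is about reaching low-income smokers, but the stated measures of dissemination success count all enrolees whatever their income

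*Protocol article*

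**What the plan says.** The section on Aim 2 says that input from San Francisco Health Network (SFHN) patients will identify "effective ways of reaching and encouraging low-income English- and Spanish-speaking smokers to use the digital smoking cessation interventions", and that this knowledge is meant to serve dissemination after the grant.

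The measures attached to that aim are these:

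- Online Study 2, on recruitment sources identified by tokens: "We will examine which of these sources yield the greatest increases in recruitment".
- Online Study 2, on recruitment as a whole: "We will also track overall recruitment, as measured by the speed with which we meet our recruitment goals".
- Hypothesis H2: recruitment using strategies derived from the ethnographic interviews "will reach a significantly higher number of participants for successive online studies".

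Online Study 3 repeats the procedure of Online Studies 1 and 2. The Measures section for the online studies gives "Eligibility: age, current smoker, speak English or Spanish". Its baseline questionnaire includes "marital status, employment status, income, and educational level". A low-income rule based on insurance status is written under recruitment for the field studies only. The data analysis section for Online Studies 1 to 3 says that observed changes, recruitment rates among them, will help set priorities for recruitment media and messages.

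**The concern.** The aim names a target group, and the measures do not look for it. A source is credited for every smoker it brings in, whether or not that smoker belongs to the group the project wants to reach. The difference matters because the Clinical Problem section gives socioeconomic disparity as the reason for the study. It reports the worry that "more highly educated people may be more likely to use these interventions", together with the team's own finding that its interventions benefit people of higher standing more.

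Two things are at stake. Effort could shift towards channels that fill places quickly with better-off smokers. H2 could also be declared met with no gain, or even a loss, in low-income smokers reached. In either case Aim 2 would seem to be answered when it had not been.

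**Working it through.** The plan gives no figure for this point, so there is nothing to reproduce. The check has three parts.

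**1. Does any other section restrict the count to low-income smokers?**

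- Online eligibility covers age, smoking and language, with no income criterion.
- The insurance-based rule sits under the field studies. The list of online baseline items contains income but not insurance.
- Tokens record the source and separate SFHN users from open recruits. SFHN visits are almost all covered by Medi-Cal or Medicare or are uninsured (71.00% + 28.60% = 99.60%), so the token partly marks the target group. It does not separate income levels among open recruits.
- The equal split by language controls language, not income.

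No section restricts the count or breaks it down by income.

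**2. How much of the sample is exposed?**

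- Online Study 1, with the procedure repeated in Online Studies 2 and 3: up to 50 + 50 = 100 open recruits and 25 + 25 = 50 SFHN recruits. The open share is 100/150 = 67%.
- RCT target: 800 open and 200 SFHN. The open share is 800/1000 = 80%.

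The sources named in Online Study 2 (social media, radio and television, public service announcements, search engine ads) are largely open channels.

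**3. When would the two counts disagree?**

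Let sources A and B bring in n_A > n_B enrolees, with low-income shares p_A and p_B. The order by low-income enrolees is the reverse of the order by all enrolees when n_B × p_B > n_A × p_A, that is, when p_B/p_A > n_A/n_B. The plan speaks of increases. The same condition holds if n is the number of added enrolees and p the low-income share among them.

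With an assumed split of the 100 open places between two sources, the order reverses when p_B/p_A exceeds:

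- 55 v 45: 55/45 = 1.22
- 60 v 40: 60/40 = 1.50
- 70 v 30: 70/30 = 2.33

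Examples at 60 v 40, with assumed shares:

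- 20% v 50%: 60 × 0.20 = 12 and 40 × 0.50 = 20. Reversed.
- 40% v 70%: 60 × 0.40 = 24 and 40 × 0.70 = 28. Reversed.
- 50% v 50%: 60 × 0.50 = 30 and 40 × 0.50 = 20. Not reversed.

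The same algebra applies to H2. If the number reached rises from N_1 to N_2 while the low-income share falls from p_1 to p_2, low-income reach does not rise unless N_2/N_1 > p_1/p_2. With an assumed fall from 70% to 40%, total reach could grow by a factor of up to 0.70/0.40 = 1.75 without one more low-income smoker.

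**The case against.** The strongest reply is that source counts are not how Aim 2 is mainly pursued. Aim 2 relies on input from SFHN patients, the ethnographic interviews guide the recruitment strategy, and the suggestions for Online Study 2 come from field-test participants, who are planned to be low-income. This is correct, and the design does use the target group to shape the messages. It does not measure who responds to them, and that is what the source comparison and H2 are for.

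A second reply is that a table of source by income is a detail an article may leave to a fuller document. The data are collected and nothing forbids the table. That would settle the matter if the article were silent. It does state the measure, however, and both the source comparison and H2 state it as a count of all enrolees.

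Third, the counts will be small. Online Study 2 names about six sources. An even split of 50 open recruits per language gives 50/6, or about 8 per source and language. At an assumed 50% low-income share that is about 4. This stands, and it limits how finely the comparison can be cut.

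Three stronger readings are tempting, and the documents do not support them:

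- A reader might infer that sources will be ranked and a winner chosen. The text says only that they will be examined. The nearest link to a decision is the statement that observed changes help set priorities for media and messages.
- A reader might infer that RCT advertising is allocated on these counts. The RCT section bases it on areas and media that reach Latinos and on published evidence about cost-effective sites, and does not mention the source comparison.
- A reader might take the Clinical Problem section as saying that open channels attract the better educated. It voices a concern about use and reports a result about benefit, and says nothing about which channel attracts whom.

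**Conclusion.** The point holds as a mismatch between aim and measure. Aim 2 concerns low-income smokers, while the source comparison, the speed of recruitment and H2 count everyone. Up to 67% of each of Online Studies 1 to 3 is recruited without an income criterion, and recruitment changes feed into priorities for media and messages. The stated measures can therefore favour sources that mainly reach better-off smokers, and H2 can be met by them.

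Whether this would happen is unknown, because the documents give no income shares by source. The reversal thresholds show only that moderate differences in share suffice when sources are close in volume. The splits and shares behind them are assumptions.

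The consequence is confined to Aim 2 and H2. The randomised comparison, H1, H3 and the sample size are untouched. The change is worth making because without it Aim 2 is not assessed in the group it names.

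**What to change.** - In Online Studies 2 and 3, compare sources on the number and the share of low-income enrolees, using baseline income and the source token. Show total enrolees as a secondary figure.
- Fix the income cut-off before Online Study 2 starts. The insurance definition used for the field studies cannot simply be carried over, because insurance is not among the listed online baseline items.
- Word H2 in the same terms, so that it refers to low-income participants reached.
- Pool Online Studies 2 and 3 for the source comparison, which gives up to 2 × 100 = 200 open recruits, and report the breakdown by language descriptively.
- Show enrolees with missing income or missing token as their own category. Participants may decline questions, and tokens have to be entered when the app is installed.

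The cost is one tabulation from items already collected and one decision on the cut-off. The price is smaller counts per source, so differences between sources should be read with caution.

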##### Online Study 3: Version 2.0

We will repeat the procedure as in Online Studies 1 and 2.

##### Online Study 4: Randomized Controlled Trial

We will carry out an RCT comparing the final version of the San Francisco Stop Smoking Web App with the baseline Web app. The RCT will be powered to detect differences in utilization rates and 7-day point prevalence quit rates, as described in the Data Analysis section. We will carry out open online recruitment, with a target of 800 smokers (400 English speakers and 400 Spanish speakers), as well as focused SFHN recruitment, with a target of 200 smokers (100 English speakers and 100 Spanish speakers).

Open recruitment will focus on California smokers. We will target English- and Spanish-speaking smokers searching for information on smoking cessation online using social media recruitment efforts, appearances on radio and television shows (especially those likely to be watched by Latinos), and a limited amount of search engine ads. To target the latter, we will use information reported by Graham and others [39] in terms of the most cost-effective online sites to recruit Latinos. We will focus our recruitment advertising resources on areas of California that have large proportions of Latinos in order to oversample Spanish-speaking smokers.

SFHN recruitment involves providing fliers for patients in waiting rooms at the San Francisco General Hospital clinics. Waiting room staff will also be given the fliers so they can inform smoking patients about the study. Primary care physicians will be provided with Post-It–like prescription pads which will have information regarding how to obtain the smoking cessation Web app. We will provide tokens (code numbers) to be entered when the Web app is installed that will indicate the source of the referral in order to determine whether physician recommendations to use the Web app result in greater utilization and higher quit rates than standard fliers. These tokens will also distinguish SFHN users from users recruited via open online recruitment.

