Participants will be randomly assigned to use either the baseline app or the final version of the San Francisco Stop Smoking Web app. We will focus our analysis on quit rates and use of the app. Latency (time spent) on content pages will be compared across the two versions of the app using independent samples *t* tests. Based on a Cohen designation of a small effect size for group mean comparisons of 0.2, a priori power analyses revealed a necessary sample size of N=800 (400 per version) to achieve a power of .80. Quit rates (smoking cessation status at 7- and 30-days) will be evaluated at 1, 3, and 6 months following registration, with individuals lost to follow-up treated as still smoking. To examine quit rate as a function of website version and demographic characteristics, logistic regression analyses will be conducted with quit status as the criterion variable; website version as the focal predictor; and gender, age, ethnicity, race, and income entered as covariates. Prior research suggests a usual care quit rate of 10% based on the 11% quit rate finding for the printed version of the *Guía Para Dejar de Fumar* in the Muñoz et al [13] study and missing=smoking rates ranging from 6.0% to 14.5% in our online studies [16,18,20]. We have estimated the quit rate of the improved, user-centered Web app at 20% based on the 23% quit rate found for the combined intervention in a later Muñoz et al study [13] and the best estimates of our online website, which yielded a missing=smoking rate of 20.2% for Spanish speakers and 21% for English speakers [16]. We estimate an increase of 10% (ie, improved website will result in 20% quit rate compared to a 10% quit rate for the baseline app), which results in an odds ratio of 2.25. This odds ratio was used as the effect size estimate in an a priori power analysis that yielded a total sample size of N=550 (225 per site version) to achieve power of .80.

We estimate needing a minimum of 800 participants to detect small effect sizes in utilization and 550 to detect clinically significant differences in quit rates. We therefore propose to recruit 800 participants via the open online recruitment process (to reach the minimum sample size estimated in our power analysis) and an additional 200 SFHN participants to increase our sample size and carry out secondary subgroup analyses to determine whether utilization and quit rates for the SFHN patients appear similar to those recruited outside the SFHN.

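### The token comparison of physician recommendation with fliers is worded as a causal question, but referral route is not randomised and is seen only for people who install the app

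*Protocol article*

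**What the plan says.** The passage is in the protocol article under Online Study 4: Randomized Controlled Trial, in the paragraph on SFHN recruitment.

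- **Fliers:** "SFHN recruitment involves providing fliers for patients in waiting rooms at the San Francisco General Hospital clinics". Staff hand them out too: "Waiting room staff will also be given the fliers so they can inform smoking patients about the study".
- **Pads:** primary care physicians are given "prescription pads which will have information regarding how to obtain the smoking cessation Web app".
- **How the source is recorded:** "We will provide tokens (code numbers) to be entered when the Web app is installed that will indicate the source of the referral".
- **Purpose of the tokens:** to determine "whether physician recommendations to use the Web app result in greater utilization and higher quit rates than standard fliers". They also separate SFHN users from those recruited openly online.

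The Data analysis section for Online Study 4 says what is randomised: "Participants will be randomly assigned to use either the baseline app or the final version of the San Francisco Stop Smoking Web app". Its one stated regression for quit status has "website version as the focal predictor; and gender, age, ethnicity, race, and income entered as covariates". Referral source is not a term in that model. No analysis of the tokens is described there, and nowhere is the pad-versus-flier question called exploratory or associational.

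**The concern.** The aim is worded as an effect of physician recommendation on use and on quitting. To answer it, the two referral groups would have to be comparable apart from the route, and the comparison would have to include the people exposed to each route. The design described secures neither.

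First, a patient's route depends on whether a physician hands over a pad and whether the patient picks up or is given a flier. If physicians tend to advise smokers who are sicker, more dependent or more ready to quit, the groups differ before they open the app.

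Second, the token exists only once the app is installed. People who received a pad or flier and did not install do not appear. If the route affects who installs, comparing installers can create a difference, or hide one, even when the patients offered each route were alike.

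At stake is what the trial may conclude on this question: a difference between tokens, or its absence, could not be credited to the physician's recommendation.

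**Working it through.** The document gives no sample size, effect size or power for this comparison, so there is no stated figure to reproduce. The check is of the design, with two illustrations of what it allows.

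**Step 1. The passages side by side.**

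| Needed for a causal answer | What the article provides |
|---|---|
| Allocation of the route | Only app version is randomised; no allocation of patients, physicians or clinics to pad or flier is stated |
| Outcome for all exposed | Source known only from a token entered at installation; no count of pads or fliers issued is described |
| Control of likely confounders | The stated model is for app version; it adjusts for gender, age, ethnicity, race and income, but not for dependence or quit confidence |

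The Measures section (Online Studies) lists cigarettes per day, the Fagerström test and a rating of quit confidence at baseline, so these variables will be available.

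**Step 2. Confounding, with no true effect of route.** Assume that motivated smokers quit at 20% and others at 10%. These two rates are borrowed from the trial's planning values; using them for motivation groups is an assumption, and so are the shares below. With a share m motivated among installers, the quit rate is 0.20m + 0.10(1 − m).

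| Motivated, pad | Motivated, flier | Quit rate, pad | Quit rate, flier | Difference |
|---|---|---|---|---|
| 60% | 40% | 16% | 14% | +2 points |
| 80% | 40% | 18% | 14% | +4 points |
| 40% | 60% | 14% | 16% | −2 points |
| 30% | 70% | 13% | 17% | −4 points |

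The apparent difference takes either sign, depending on whom physicians choose to advise.

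**Step 3. Selection on installation, with identical patients and no true effect on quitting.** Assume that 30% of those offered either route are motivated, with the same quit rates as in Step 2. Assume install rates (motivated, others) of 50% and 30% with pads, and 30% and 5% with fliers.

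- Pads: the installing share is 0.30 × 0.50 + 0.70 × 0.30 = 0.15 + 0.21 = 0.36. The quit rate among installers is (0.15 × 0.20 + 0.21 × 0.10) / 0.36 = 0.051 / 0.36 = 14.2%.
- Fliers: the installing share is 0.30 × 0.30 + 0.70 × 0.05 = 0.09 + 0.035 = 0.125. The quit rate among installers is (0.09 × 0.20 + 0.035 × 0.10) / 0.125 = 0.0215 / 0.125 = 17.2%.

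Here the pad only raises uptake, yet pad users appear to quit 3.0 points less often. Other install rates would give other answers. The example shows that the problem is possible, not how large it is in this trial.

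**The case against.** The best defence is that this is a side question in one sentence. It is not one of the three aims or three hypotheses, and the Data analysis section gives the SFHN sample another purpose: to see whether its rates look similar to those of people recruited elsewhere. No test or decision rule is fixed for the tokens, and a condensed article may leave the model to the statistical analysis plan. This stands as to weight and is why the severity is low. It does not remove the point, because the article itself fixes the causal wording and the way the source is recorded. An analysis plan can add adjustment, but it cannot supply allocation or recover the people who never installed.

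A reader might also infer more than the text supports:

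- **That many pad recipients also see a flier in the same waiting room, and that one token cannot show both.** Fliers are placed at San Francisco General Hospital clinics and pads go to primary care physicians. The article describes 14 primary care clinics across the city besides the hospital and does not say that the sites coincide. Nor does it say whether more than one token can be entered.
- **That a wrong answer would misdirect dissemination.** Aim 2 rests on input from SFHN patients, and H2 concerns numbers recruited. No passage makes a dissemination decision depend on quit rates by token.
- **That the small SFHN sample shows bias.** The target of 200 smokers limits precision and is a reason to report confidence intervals. Low power says nothing about the size of bias.

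**Conclusion.** The point holds in a limited form. The comparison as described is non-randomised and restricted to installers, so it cannot support the causal answer its wording promises. It cannot be assumed unbiased.

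The stronger statement, that the result will be biased by some amount or in a given direction, is not supported. No passage shows how pad and flier patients differ or how many of each install. The differences of 2 to 4 points either way, and of 3 points from selection alone, rest entirely on assumed motivation shares, quit rates and install rates.

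The randomised comparison of the final app with the baseline app is untouched. Severity is low: it concerns the wording and analysis of a secondary question.

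**What to change.** In the SFHN recruitment paragraph of Online Study 4, replace the causal aim with a descriptive one: to estimate the association between referral token and utilization and quit rates among SFHN participants who install the app, reported with confidence intervals. Adjust for randomised app version and for baseline Fagerström score, cigarettes per day and quit confidence. State that no causal conclusion about physician recommendation will be drawn, since adjustment for these variables cannot account for unmeasured differences or for people who did not install.

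The cost is a change of wording and one adjusted model for each outcome, using data already planned for collection. The downside is a weaker claim. The recruitment procedure need not change.
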